## 2.2 Primary Objective

To determine if pre-exposure prophylaxis (PrEP) with 400mg hydroxychloroquine (HCQ), taken orally once daily reduces microbiologically confirmed COVID-19 among front line health care workers at high risk for SARS-CoV-2 exposure.

## 2.3 Secondary Objective(s)

1. To compare the following secondary outcomes between study arms:
  - Adverse events
  - Duration of symptomatic COVID-19
  - Days hospitalized attributed to COVID-19
  - Respiratory failure attributable to COVID-19 requiring i) non-invasive ventilation or ii) intubation/mechanical ventilation
  - Mortality attributed to COVID-19
  - Number of days unable to work attributed to COVID-19
  - Asymptomatic COVID-19
  - Ability of participant plasma to neutralize SARS-CoV-2 virus (plaque reduction neutralization test) *in vitro*
2. To explore laboratory markers within participants with confirmed COVID-19:
  - Severity markers of host immune and endothelial activation measured at clinical presentation and their ability to predict severity and outcome
3. To describe short-term psychological distress associated with risk of COVID-19 exposure at 1, 60, 120 days of the study.

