|---------------------------|-------------------------------------------------------------------------------------------------------------------------------------------------------------------------------------------------------------------------------------------------------------------------------------------------------------------------------------------------------------------------------------------------------------------------------------------------------------------------------------------------------------------------------------------------------------------------------------------------------------------------------------------------------------------------------------------------------------------------------------------------------------------------------------------------------------------------------------------------------------------------------------------------------------------------------------------------------------------------------------------------------------------------------------------------------------------------------------------------------------------------------------------------------------------------|
|                           | 
 
• Respiratory failure attributable to COVID-19 requiring i) non-invasive ventilation or ii) intubation/mechanical ventilation
 
• Mortality attributed to COVID-19
 
• Number of days unable to work attributed to COVID-19
 
• Seroconversion (COVID-19 negative to COVID-19 positive over the study period)
 
• Ability of participant plasma to neutralize SARS-CoV-2 virus (plaque reduction neutralization test) in vitro
 
 
To explore laboratory markers within participants with confirmed COVID-19:
 
 
• Circulating markers of host immune and endothelial activation in participant plasma and their correlation with disease severity and outcome
 
 
To describe short-term psychological distress associated with risk of COVID-19 exposure at 1, 60, 120 days of the study.
                                                                                                                                                                                                                                   |

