## 8.0 CLINICAL AND LABORATORY EVALUATIONS

### 8.1 Clinical Evaluations

All in-person study visits will begin with a COVID-19 symptom screen (see Questionnaire Content document). If the participant fails the symptom screen, a surgical mask should be placed on the participant and full droplet/contact precautions will be followed by study staff (i.e. surgical mask, eye protection, gown, glove). Any participant screening positive for symptoms of COVID-19 will then be directed to the most appropriate place for a confirmatory COVID-19 test (within the department or occupational health as per site institutional guidelines).

For all COVID-19 screen negative participants, study staff will conduct brief interviews to document medical history (baseline comorbidities and medications at day 1 and then new comorbidities, medications, adverse events and side effects at day 30,60,90,120). No physical examinations are required in this study. All WOCs will have a screening urine test at Day 1, 30, 60 and 90. All participants will have a review of a baseline QTc interval measure at Day 1 and a repeat QTc measure at Day 30, 60, 90 and 120. Participants

with a baseline QTc between 430-450 ms will be referred for a repeat QTc measure within 72 hours of commencing study drug.

All side effects will be documented by the study coordinator. The study coordinator has experience in implementing clinical trials of investigational agents and collecting and documenting AEs/SAEs. It is the study physician who will assess severity and relationship to study drug. If the side effect is attributed to the study tablet and has an impact on the participant's functional status (ex. ability to work) or general state of well being, the Study Physician will be responsible for further follow up. Ultimately, the participant will be supported in any decision they make regarding the continuation of study tablets.

If a participant becomes COVID-19 positive at any time in the study, all further in-person clinical evaluations will occur remotely (via telephone call) in light of necessary self-isolation and reducing risk to study staff. They will not have further respiratory specimens or phlebotomy collected while they have symptomatic COVID-19.

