#### 8.2.3 SARS-CoV-2 Serology

Methods for serologic testing of COVID-19 are still in development worldwide at the time of writing, but are rapidly emerging. Participants will undergo venipuncture at baseline, and monthly until and including the 120 day visit and samples processed into plasma for frozen storage by [name] laboratory (co-PI). Frozen samples will be batch-tested in the laboratory of Co-I [name] at the conclusion of the study when methods are finalized.

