#### 8.2.5 Biomarkers of disease severity

Plasma samples (minimum required volume of 250 µL) collected from participants at study enrolment and scheduled study visits will be processed via a custom multiplex Luminex®-based assays or ELISA to quantify plasma levels of markers of host response

to infection including inflammation, gut-leak, and endothelial activation in the laboratory of [name]. Analytes include Angiopoietin (Ang)-1, Ang-2, soluble Tyrosine kinase with immunoglobuline-like and EGF-like domains (sTIE)1, sTIE2, Vascular Endothelial Growth Factor (VEGF), soluble VEGF-receptor1, soluble Endoglin (sEng), soluble Intercellular Adhesion Molecule (sICAM), soluble Tumour Necrosis Factor (sTNF) receptor 2 (sTNFR2), C5a, Chitinase-3-like protein 1 (CHI3L1), C-reactive protein (CRP), Interleukin (IL)-18 binding protein (IL-18BP), IL-6, Zo-1, zonulin, Lipopolysaccharide-binding protein (LBP) ,and Intestinal fatty acid binding protein (I-fabp). Proteins were selected based on evidence of a critical role of in inflammatory pathways that mediate disease severity.

UHN and U of T Biosafety have approved sample handling and the testing procedure for this study.

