## Special Schedule Considerations:

**If any participant is under quarantine for suspected COVID-19 (ie they are awaiting confirmatory testing results) and, therefore, unable to make a study visit in a visit window,** a remote visit will occur and every effort will be made to have an in-person study visit scheduled as soon as they are cleared as negative for COVID-19 for sample collection.

**If any participant is confirmed COVID-19 positive during the study, the above scheduled visits will continue *remotely* (telephone) and the weekly email questionnaire will continue.** During the time in which they are symptomatic and under isolation, the following events will be suspended: dispensation of drug, self-collected viral detection sample, venous blood draw. COVID-19 positive participants who have recovered and have been deemed safe to return to work by their institution will be asked to return to the above study schedule.

**COVID-19 positive participants who have been deemed safe to return to work will be given the option of either a) resuming their blinded study drug and then entering the open-label extension at day 90 as previously scheduled, or b) starting the 30-day open-label extension immediately.** The rationale for providing the option to resume blinded study drug is that it remains unknown whether individuals who recover from COVID-19 infection remain susceptible to re-infection, and acquiring COVID-19 does not necessarily mean that the blinded study drug that the participant had been using was not providing partial protection. The rationale for providing the option to skip immediately to the open-label extension is that some participants may understandably prefer to abandon their study drug under these circumstances, and the study has committed to providing every participant with a one-month open-label extension.

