#### 9.4 Study Visits 1-4 (Follow-up at Day 30, 60, 90, and 120): Conducted in person.

Participants will be schedule for monthly Study Visit appointments. These are expected to take a maximum of 30 minutes, and in many cases much less. Whenever possible, the study visits will be coordinated with the participant's scheduled ED shift in order to minimize travel and burden on the participant. The components of the Study Visit are as follows:

- **Interview:** The coordinator will review the participant's COVID-19 symptom reporting, their responses to the Adverse Events Questionnaire and Tolerability Questionnaire. The research coordinator will review the responses prior to releasing the next installment of study drug/placebo. If the participant has any concern regarding adverse events or other aspect of the study, they will have the opportunity to discuss these with the research coordinator during the visit.
- **Urine pregnancy test:** for women of childbearing potential.
- **Self-collected viral detection sample:** As above.
- **Blood for serology and other laboratory markers:** As above.
- **QTc interval evaluation:** The QTc will be measured and recorded.
- **Dispense study drug:** The coordinator must confirm receipt of the package with the participant, and review dosing.
- **Psychological distress questionnaire:** will be emailed to participant to complete at day 60 and day 120.

Participants with confirmed COVID-19 will be asked to discontinue their study tablets (see Section 6.7). They will not present for in person visits until they are cleared to return to work.

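### Objective 2 in Section 2.3 asks for severity markers at clinical presentation, but the protocol plans no blood draw at that time

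*Protocol*

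**What the plan says.** Protocol Section 2.3, objective 2, concerns laboratory markers in participants with confirmed COVID-19: "Severity markers of host immune and endothelial activation measured at clinical presentation and their ability to predict severity and outcome". The synopsis gives the same objective with no timing and with correlation in place of prediction: "Circulating markers of host immune and endothelial activation in participant plasma and their correlation with disease severity and outcome".

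The sampling rules are these:

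- Section 8.2.5, which implements the objective, uses plasma "collected from participants at study enrolment and scheduled study visits".
- Section 8.2.3 gives the blood schedule: "Participants will undergo venipuncture at baseline, and monthly until and including the 120 day visit". Table 1 in Section 9.1 agrees (Days 1, 30, 60, 90 and 120) and shows no draw triggered by illness.
- Section 8.1, on participants who become positive: "They will not have further respiratory specimens or phlebotomy collected while they have symptomatic COVID-19".
- The Special Schedule Considerations in Section 9.1, for the time a confirmed case is symptomatic and isolated: "the following events will be suspended: dispensation of drug, self-collected viral detection sample, venous blood draw".
- Section 9.4, on confirmed cases: "They will not present for in person visits until they are cleared to return to work".
- Section 2.4 sends symptomatic workers to routine occupational health, emergency department or ministry testing. The study collects the results, and no study blood draw is described there.

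**The concern.** A marker measured at presentation describes the host response when the participant first presents ill, before the course of the disease is known. That timing is what would make it a possible early predictor of severity. The planned samples answer other questions. A pre-illness sample shows the participant's state before symptoms, possibly during incubation. A post-recovery sample comes after the outcome it would be meant to predict.

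The post-recovery sample is also selective. In-person visits resume only after clearance to return to work, so participants who die or stay ill contribute none. Whether the sample exists depends on the severity under study.

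If results from these samples were reported under the Section 2.3 wording, readers would take them for early predictors of severity.

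**Working it through.** The point is a comparison of sections. The protocol gives no figure for the number or timing of these samples, so there is none to reproduce.

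**Step 1. What each type of case yields**

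| Situation | Rule | Plasma available |
|---|---|---|
| Before illness | Monthly draws (8.2.3, Table 1) | Last scheduled sample |
| Suspected, in quarantine, unable to attend a visit | Remote visit; in-person sampling once cleared as negative (Special Schedule Considerations) | None while suspected |
| Symptomatic, not yet confirmed, attending a scheduled visit | Droplet precautions (7.2, 8.2.1), then directed to testing (8.1) | Not planned; possible by chance |
| Confirmed and symptomatic | No phlebotomy (8.1, 9.1); no in-person visit (9.4) | None |
| Recovered and back at work | Schedule resumes (9.1) | Convalescent sample |
| Asymptomatic, positive on the viral sample of a monthly visit | Viral sample and blood on the same day (Table 1) | Same-day plasma, but no clinical presentation |

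No row gives a planned sample at clinical presentation. Section 8.2.4 fits this: for infected participants the plaque assay relies on plasma already drawn at earlier monthly visits.

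**Step 2. Gap from the last sample to onset**

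Visits are nominally 30 days apart, so the gap is up to about 30 days. If onset is uniform between visits (assumed), the mean is 30 / 2 = 15 days. Table 1 allows ±7 days at Days 30 to 120. A Day 30 visit held on Day 30 − 7 = 23 and a Day 60 visit held on Day 60 + 7 = 67 are both in window and 67 − 23 = 44 days apart. The gap can therefore reach 44 days with no visit missed.

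**Step 3. Upper bound on chance draws near presentation**

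Assume that a draw near presentation happens only if a monthly visit falls within the w days between symptom onset and confirmation or isolation. The probability is about w / 30. Section 11.2 gives 92 events. Taking all of them as symptomatic (assumed, and an overcount) gives:

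- w = 1 day: 1 / 30 = 3.3%; 92 × 1 / 30 = 3.1 participants
- w = 3 days: 3 / 30 = 10%; 92 × 3 / 30 = 9.2 participants

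The window of 1 to 3 days is an assumption; the protocol gives none. The rule for suspected cases would lower these counts. So would Section 8.1, which sends screen-positive participants for testing and describes the study interview only for screen-negative ones.

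**Step 4. Denominator**

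Section 2.4 counts any positive validated assay or seroconversion as the primary outcome, so 92 includes asymptomatic infections. The protocol gives no expected number of symptomatic cases.

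**The case against.** The strongest reply is that this is a wording slip in an exploratory aim. Objective 2 sets out to explore. Biomarkers are not among the outcome measures in Section 2.4, and Section 11.3.2 gives no biomarker analysis. Section 8.2.5 states openly where the plasma comes from, and nothing says the samples will be presented as something else. The synopsis already has wording that the planned samples can serve. All of this stands, and it limits the consequence.

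A reader might also infer that there will be no presentation samples at all and that some 90 cases are lost to the objective. The documents do not support that. The bar on phlebotomy in Section 8.1 applies to participants who have become positive, while Sections 7.2 and 8.2.1 provide for contact with symptomatic participants under droplet precautions, so a chance draw before confirmation is not excluded. The 92 events are all infections. And an asymptomatic infection detected at a monthly visit has same-day plasma, so the samples are not only pre-illness or post-recovery.

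The contradiction remains. A few accidental draws do not implement an objective, and asymptomatic infections have no clinical presentation. Nor can the matter be left to a statistical analysis plan, since no analysis can supply a sample that the protocol does not collect.

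**Conclusion.** The contradiction is real. As worded in Section 2.3, the objective cannot be met for symptomatic cases: no presentation sample is planned, and chance would supply perhaps 3 to 9 at most under the assumptions of Step 3. What can be studied is how pre-illness plasma relates to later severity, together with same-day plasma from asymptomatic infections detected at a monthly visit and a convalescent sample from those who recover. The synopsis objective is compatible with that; the Section 2.3 objective is not.

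That no presentation draw is planned rests on the text alone. The 44-day figure rests on the Table 1 windows. The 15-day mean and the 3 to 9 count rest on stated assumptions and give scale only. The issue is confined to an exploratory secondary objective; the comparison of arms, the primary endpoint, the sample size and the error rates are untouched. It should be corrected because it changes what may be concluded from the marker data.

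**What to change.** 1. In Section 2.3, remove the presentation timing and the claim of prediction, and use the synopsis wording, which concerns the correlation of circulating markers with severity and outcome.
2. Name the last scheduled sample before infection as the main marker measurement, with the time from that sample to symptom onset as a covariate. Where there are no symptoms, use the time to the first positive test.
3. Report same-day samples from asymptomatic infections separately.
4. Label any post-recovery sample as convalescent and use it descriptively only, stating that it exists only for participants who recovered and returned. A change from Day 1 to that sample should not be analysed as a marker of severity, because the most severe cases would be missing.

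The cost is a change to one objective and a short analysis note, with no new sampling and no change to the handling of ill participants. The objective gives up any claim to early prediction of severity, which the planned samples could not support.

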## 2.4 Outcome measures

The **primary outcome is microbiologically confirmed COVID-19 (SARS-CoV-2 infection)**. This is a composite endpoint which includes any positive result from a validated SARS-CoV-2 diagnostic assay including detection of viral RNA, or seroconversion by day 104 (14 days after end of the randomization period).

The microbiologic outcome measures will be obtained from validated diagnostic assays performed on participant samples (viral detection samples or blood) collected at defined intervals over the course of the study (see Section 9.1 and Table 1, Schedule of Events). Symptomatic outcome measures, clinical outcomes (ex. hospitalization, need for supported ventilation), days unable to work etc. will be collected by self-report *via* weekly email survey (see Section 9.1 Table 9.1, Schedule of Events). In the case of death or other condition rendering the participant unable to communicate or complete the weekly email survey, the outcome will be obtained by contacting the designate identified by the participant at enrollment. If it is not possible to reach this person, the participant will be considered lost to follow up.

Per Public Health Agency of Canada, Public Health Ontario, and hospital guidelines, during this COVID-19 pandemic, all HCWs must report to occupational health and their departmental supervisors and self-isolate (i.e. they must not come to work) should they develop any signs or symptoms of COVID-19, at which time they will be prioritized for testing either in the emergency department or at occupational health (and less frequently at MOH testing centres), as per site institutional guidelines. Diagnostic testing will be prompted by symptoms and be conducted according to these routine channels. Results of these tests will be collected by the data collection measures in this study.

### **Secondary outcomes measures are:**

- a) **Adverse events:** as defined using the DAIDS Table for Grading the Severity of Adverse Events, until day 120^27
- b) **Symptom duration of COVID-19:** measured in days.
- c) **Days of hospitalization attributable to COVID-19:** The number of days (or partial days) spent admitted to an acute care hospital during the study period.

- d) **Respiratory failure requiring ventilatory support attributable to COVID-19:** The number of days (or partial days) requiring i) non-invasive and ii) endotracheal intubation with ventilation during the study period.
- e) **Mortality** attributable to COVID-19 and all-cause mortality during the study period.
- f) **Number of days ineligible/unable to work due to COVID-19:** measured from symptom onset to return to work date.
- g) **Seropositivity:** reactive serology by day 120.
- h) **Short-term psychological impact of exposure to COVID-19** will be measured at the beginning of randomization (day 1), during the randomized period (day 60) and during the open-label period (day 120) using the K10, a validated measure of non-specific psychological distress, with a standard cutoff score of  $\geq 16$ .

## 3.0 SELECTION AND ENROLLMENT OF PARTICIPANTS

### 3.1 Number of Participants

The trial will enroll 988 participants across all five hospital sites in Toronto, Canada.

### 3.2 Inclusion Criteria

1. Health care worker (HCW) in clinical areas that pose high risk of exposure, who is anticipated to work at least 10 shifts over the duration of the study period (minimum 6 hours per shift) and anticipated to remain in their unit for the duration of the study (i.e., not transferring to another unit).

*For the purposes of the study:*

- *“front line health care workers” are physicians (including residents), nurses, nurse practitioners, physician assistants, respiratory therapists, X-ray technicians, social workers and support staff (including but not limited to house-keeping, and porters).*
- *“high risk of SARS-CoV-2 exposure” refers to units and/or teams expected to provide care to patients with COVID-19 and where the provision of this care is anticipated to require either aerosol generating medical procedures (AGMPs) or exposure to pre-symptomatic (i.e. unidentified) COVID-19*

*positive patients including (but not limited to) the Emergency Department, intubation response teams, Intensive Care Units, and response teams for Long Term Care (LTC) facilities and shelters served by participating hospital staff.*

2. Age  $\geq 18$  years.
3. Ability to communicate with study staff in English

